**4. Clinical Outcomes**

(1) Respiratory support escalation within 24 hours after bronchoscopy;

(2) Intubation rates within 24 hours, 7 days, and 28 days;

(3) ICU length of stay;

(4) Hospital length of stay;

(5) All-cause mortality at 28, 60, and 90 days.

**STATISTICAL ANALYSIS**

All statistical analyses will be performed according to the predefined Statistical Analysis Plan (SAP). Analyses will follow the intention-to-treat principle, with additional per-protocol analyses conducted as appropriate.

Descriptive statistics will be used to summarize baseline characteristics. Categorical variables will be compared using the chi-square test or Fisher’s exact test, and continuous variables will be analyzed using t-tests or Mann–Whitney U tests, as appropriate.

The primary outcome (escalation of respiratory support within 24 hours) will be analyzed using logistic regression The key secondary outcome (respiratory support escalation assessed hierarchically) will be analyzed using the win ratio method in a prespecified fixed-sequence hierarchical framework to prioritize endpoints and control for multiplicity. Time-to-event outcomes will be analyzed using Kaplan–Meier survival curves and log-rank tests.

All statistical tests will be two-sided, and a p-value <0.05 will be considered statistically significant.

Details of sample size calculation, sensitivity analyses, and handling of missing data are provided in the SAP.

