**OBJECTIVES**

**Primary Outcome**

To determine whether modified HFNC oxygen therapy, using a single-prong cannula interface, reduces the need for escalation of respiratory support within 24 hours after bronchoscopy in patients with ARF compared with standard oxygen therapy (SOT).

Escalation was defined as meeting any of the following criteria:

1. Requirement for invasive mechanical ventilation (IMV);

2. Requirement for non-invasive ventilation (NIV);

3. Requirement for HFNC oxygen therapy;

4. An increase in support parameters without changing the level of respiratory support: For NIV patients: a >20% increase in inspiratory positive airway pressure (IPAP), expiratory positive airway pressure (EPAP), or the fraction of inspired oxygen (FiO_2_); For HFNC oxygen therapy patients: a >20% increase in flow rate or FiO_2_; For low-flow nasal cannula oxygen therapy patients: a >50% increase in oxygen flow rate.

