**Other outcomes**

1. To evaluate whether modified HFNC oxygen therapy reduces the rate of endotracheal intubation at 24 hours, 7 days, and 28 days after bronchoscopy.

2. To assess whether modified HFNC oxygen therapy improves oxygenation stability, as measured by peripheral oxygen saturation (SpO_2_) levels during bronchoscopy.

3. To determine whether the use of modified HFNC oxygen therapy is associated with a reduced incidence of procedural interruptions during bronchoscopy.

4. To assess whether modified HFNC oxygen therapy shortens the procedure duration compared with SOT.

5. To assess the impact of modified HFNC oxygen therapy on ICU and hospital length of stay.

6. To evaluate whether modified HFNC oxygen therapy reduces all-cause mortality at 28 days, 60 days, and 90 days.

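### The 24-hour primary definition omits death, and raw length of stay counts an early death as a short stay

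*Protocol*

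**What the plan says.** The Primary Outcome section asks whether the intervention "reduces the need for escalation of respiratory support within 24 hours after bronchoscopy in patients with ARF". It continues: "Escalation was defined as meeting any of the following criteria", followed by four items: invasive ventilation, non-invasive ventilation, HFNC, or a rise in support settings at an unchanged level of support. Death is not an item. The Statistical Analysis section then states: "The primary outcome (escalation of respiratory support within 24 hours) will be analyzed using logistic regression".

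Among the Other outcomes, item 5 is "To assess the impact of modified HFNC oxygen therapy on ICU and hospital length of stay", and item 1 asks whether the intervention "reduces the rate of endotracheal intubation at 24 hours, 7 days, and 28 days after bronchoscopy". Neither comes with a rule for patients who die. For continuous variables the Statistical Analysis section says "continuous variables will be analyzed using t-tests or Mann–Whitney U tests, as appropriate".

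Mortality is a separate outcome at 28, 60 and 90 days (Other outcomes, item 6; Clinical Outcomes). No 24-hour mortality outcome is listed. The Statistical Analysis section says that analyses follow a SAP. The details it refers there by name are sample size, sensitivity analyses and missing data.

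**The concern.** A binary outcome puts every analysed patient on one side or the other. Because the list is closed, a patient who dies within 24 hours without a recorded step-up, for example after a sudden arrest or under treatment limits, falls on the good side. None of the listed exclusions concerns treatment limits. No other listed outcome would show the misclassification, because mortality is first reported at day 28.

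Length of stay has the same fault in a more consequential form. A stay ended by death is not comparable with a stay ended by recovery, yet a t-test or Mann–Whitney U test on raw days treats the shorter of the two as less stay whatever its cause. The protocol's own objective is to see whether the intervention lowers mortality. If it does, the stay comparison is pushed against the intervention by the benefit being sought; if mortality rises, the comparison flatters it.

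**Working it through.** The protocol states no sample size, event rate or mortality rate, so there is no figure to reproduce. Every rate below is an assumption chosen to show direction and size.

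**Primary outcome.** Let q be the share of an arm that dies un-escalated within 24 hours and e the escalation risk in the rest. As written, the arm's risk is (1 − q)e. With death counted it is (1 − q)e + q. The risk difference therefore changes by exactly q(HFNC) − q(SOT). Taking e = 20% for HFNC and 40% for SOT:

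- q = 2% in HFNC only: as written 0.98 × 20% − 40% = −20.4 points; with death counted 21.6% − 40% = −18.4 points.
- q = 2% in SOT only: as written 20% − 0.98 × 40% = −19.2 points; with death counted 20% − 41.2% = −21.2 points.
- q equal in both arms (0.5%, 1%, 2% or 5%): the two definitions give the same difference.

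**Length of stay, by arithmetic.** Assume lognormal stays (log-scale SD 0.6), median 12 days in survivors and 6 days in those who die, the same in both arms, with mortality 30% versus 20%. The mean of such a distribution is median × exp(0.6²/2) = median × 1.197, so 14.4 and 7.2 days.

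- Arm with 30% mortality: 0.7 × 14.4 + 0.3 × 7.2 = 12.2 days.
- Arm with 20% mortality: 0.8 × 14.4 + 0.2 × 7.2 = 12.9 days.

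The medians are 9.9 and 10.6 days. The arm with fewer deaths looks worse although nothing about stay differs. Mean ICU-free days to day 28, with death scored 0, are 10.1 and 11.5, which point the right way.

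**Length of stay, by simulation.** Survivors' median 14 days, deaths' median 6 days, same spread, 100 per arm, 4,000 replicates, two-sided Mann–Whitney U at 0.05. The last two columns give the share of trials significantly favouring the arm with more deaths (in the first row, one given arm).

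| Mortality | Mean difference in median stay (days) | Raw stay | Death ranked worst |
|---|---|---|---|
| 15% vs 15% | 0.0 | 2.4% | 2.6% |
| 20% vs 15% | −0.5 | 5.5% | 0.3% |
| 25% vs 15% | −1.0 | 13.4% | 0.2% |
| 30% vs 15% | −1.5 | 23.3% | 0.0% |
| 35% vs 15% | −2.0 | 39.0% | 0.0% |

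With equal mortality the overall rejection rate on raw stay is 5.0%, so the excess in the other rows comes from the mortality difference alone.

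**Intubation at 28 days.** Assume constant hazards: an intubation hazard that gives 20% if nobody died, and a death hazard that gives risk d on its own. The crude rate is h_i/(h_i + h_d) × [1 − 0.8(1 − d)]. For d = 10% this is 0.679 × 0.28 = 19.0%. For d = 20% it is 0.5 × 0.36 = 18.0%. For d = 30% it is 0.385 × 0.44 = 16.9%. With an identical intubation hazard, the arm with more deaths gains 1 to 2 points.

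**The case against.** The strongest reply is that much of this belongs to the SAP, which is not at hand. How deaths enter length of stay and the later intubation rates is commonly set there, and the protocol's silence does not prove that they are mishandled. That stands in part: the SAP may contain a rule for stay. It does not rescue the primary outcome, whose definition the protocol itself fixes as a list. Nor is a known death missing data, so the referral of missing-data handling to the SAP does not cover it.

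A second reply is that the 24-hour effect is small. That also stands. Anyone given invasive ventilation, NIV, HFNC or a qualifying rise in settings before death is already an event, and patients with limits on intubation can still meet the other criteria. A reader might infer that early death is in general scored as a success; the definition supports this only for deaths with no escalation at all.

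A third reply is that length of stay is only one of the other outcomes and that mortality is reported beside it. This limits the consequence. It does not make the test interpretable.

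Two further inferences are tempting and not supported. One is that Kaplan–Meier will censor deaths in the intubation analysis and overstate its incidence. The protocol says "Time-to-event outcomes will be analyzed using Kaplan–Meier survival curves and log-rank tests" without naming the outcomes. Intubation is stated as a rate at fixed times, and with complete follow-up the crude proportion already estimates the cumulative incidence. The other is that the win ratio leaves death out. The protocol says "The key secondary outcome (respiratory support escalation assessed hierarchically) will be analyzed using the win ratio method" but does not list the tiers, so death may already be one.

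**Conclusion.** The point holds in two parts of unequal weight. The primary definition, followed as written, counts an un-escalated death within 24 hours as a favourable outcome. The resulting shift in the risk difference equals the between-arm difference in such deaths: zero if they are balanced, 2 points if an assumed 2% fall in one arm only. It is probably small, but it is a fault in the definition itself.

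Raw length of stay tested by t-test or Mann–Whitney U depends on survival. Under the assumed 10-point mortality gap (25% versus 15%, 100 per arm), median stay differs by about 1 day with no difference among survivors, and 13.4% of trials significantly favour the arm with more deaths. What this shows is a null effect on stay turning into an apparent one; its size rests entirely on assumed mortality and on deaths coming earlier than discharges. The conclusion on stay would be withdrawn if the SAP already sets a suitable rule.

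For 7- and 28-day intubation, the crude rate is a legitimate quantity that needs to be read beside mortality; it is not an error.

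**What to change.** 1. In the Primary Outcome definition, add death from any cause within 24 hours of bronchoscopy as a fifth qualifying event. Check that the win-ratio order agrees with it, so that a patient who dies cannot rank above one who was escalated and survived.
2. Replace the test on raw ICU and hospital stay by days alive and out of ICU, and out of hospital, to day 28. Score death by day 28 as 0, or rank it below every survivor, which separates it from survivors still admitted at day 28. Give raw stay descriptively, by survival status. If the SAP already has an equivalent rule, cite it in the protocol.
3. For 7- and 28-day intubation, at most report intubation-or-death alongside the crude rate. No competing-risk test is needed on top of that composite, because death is then part of the event.

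The cost is wording, a slightly broader primary composite and one changed outcome among the other outcomes. The protocol lists mortality at fixed days and lengths of stay but no dates, so confirm that the case report form records the date and time of death and the discharge dates.

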**Step 5: Bronchoscopy procedure**

Bronchoscopy will be performed via nasal access following standard clinical practice. Diagnostic interventions such as bronchoalveolar lavage (BAL), bronchial brushing, endobronchial biopsy, or transbronchial lung biopsy will be performed when clinically indicated. Any procedural interruption or adverse events will be documented in real time. Vital signs and EIT parameters will be recorded at five predefined time points: T0, before bronchoscopy; T1, upon insertion of the bronchoscope into the nasal cavity; T2, at the end of the procedure; T3, 10 minutes after bronchoscopy; and T4, 2 hours after bronchoscopy.

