**2. Procedural data**

(1) Type of bronchoscopy and diagnostic interventions: BAL, bronchial brushing, endobronchial biopsy, transbronchial lung biopsy;

(2) Volume of BAL fluid instilled and recovered;

(3) Duration of bronchoscopy;

(4) Vital signs, including respiratory rate, heart rate, mean arterial pressure, and SpO_2_, as well as EIT measurements such as tidal impedance variation (TIV) and changes in end-expiratory lung impedance (ΔEELI), will be recorded at five predefined time points: T0, T1, T2, T3, and T4;

(5) Arterial blood gas analysis at T4.

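### The only test named for continuous outcomes cannot use baseline SpO2 or site, and the SpO2 objective has no single designated measure (minor)

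*Protocol*

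**What the plan says.** The Statistical Analysis section first says "Descriptive statistics will be used to summarize baseline characteristics". It then gives a test for categorical variables and says that "continuous variables will be analyzed using t-tests or Mann–Whitney U tests, as appropriate". Logistic regression is named for the primary outcome, the win ratio for the key secondary outcome, and Kaplan–Meier curves with log-rank tests for time-to-event outcomes. No other method is named for a continuous variable. The section closes with "All statistical tests will be two-sided, and a p-value <0.05 will be considered statistically significant". Multiplicity is mentioned only in connection with the win ratio.

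Objective 2 under Other outcomes asks whether the intervention "improves oxygenation stability, as measured by peripheral oxygen saturation" levels during bronchoscopy. Under Data Collection, vital signs including SpO2, together with EIT measures, "will be recorded at five predefined time points: T0, T1, T2, T3, and T4". The lowest SpO2 during the procedure is recorded separately among the procedural events.

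Step 2 of the Study Procedures collects baseline vital signs. Randomisation follows at Step 3, stratified by site, and the assigned oxygen is started at Step 4.

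**The concern.** A two-sample t-test or Mann–Whitney U test has no place for a covariate. Applied to SpO2, it leaves unused a value measured before allocation and the factor on which the randomisation was stratified. The cost is lost precision, not bias.

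The second part is the choice of measure. Objective 2 states a concept, stability of oxygenation, but not the variable that represents it. SpO2 at scope insertion (T1), SpO2 at the end of the procedure (T2) and the lowest SpO2 each fit its wording, and each could be tested at 0.05. If the choice is left until the data are seen, the most favourable of the three could be reported as the answer to the objective.

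**Working it through.** The protocol states no sample size, SD, correlation or number of tests for these measures, so there is no figure of its own to reproduce.

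**Which SpO2 values bear on objective 2.** The objective is limited to the procedure itself. The timing of the readings begins "T0, before bronchoscopy; T1, upon insertion of the bronchoscope into the nasal cavity"; T2 is the end of the procedure, T3 is 10 minutes after it and T4 is 2 hours after it. T0, T3 and T4 therefore fall outside the procedure. T1, T2 and the lowest SpO2 remain: 3 candidates.

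**False-positive chance over the three.** With no true effect and α = 0.05 each:

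- Independent tests: 1 − 0.95³ = 1 − 0.857 = 0.143, about 14%.
- The three values come from the same patient in one procedure and are likely to be positively correlated, which lowers this figure. About 14% is therefore best read as an upper value.

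**Is there a clean baseline?** Step 2 precedes randomisation, and the Data Collection section counts SpO2 among the vital signs. Reading Step 2 vital signs as including SpO2 is therefore natural, though Step 2 does not list them one by one. T0 is different: it is before bronchoscopy, but the protocol does not say whether it is before or after the assigned oxygen is started at Step 4. If after, T0 may already carry part of the treatment effect.

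**Precision gained by adjustment.** With r the correlation between baseline and outcome, ANCOVA leaves a residual variance of about (1 − r²) times the unadjusted variance. The equivalent gain in sample size is 1/(1 − r²). For a comparison that would have 80% power unadjusted (an illustration, not a protocol figure), adjusted power is Φ[(1.960 + 0.842)/√(1 − r²) − 1.960].

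| Assumed r | Variance factor 1 − r² | Sample-size equivalent | Power if 80% unadjusted |
|---|---|---|---|
| 0.3 | 0.91 | 1.10 | 83.6% |
| 0.5 | 0.75 | 1.33 | 89.9% |
| 0.7 | 0.51 | 1.96 | 97.5% |

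The range of r is an assumption. The lower end deserves weight for SpO2: the Step 2 value precedes the study device, and oxygen is then titrated in both arms to keep SpO2 above 90%, which weakens the link between baseline and later values.

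**The case against.** The strongest reply is that the sentence on t-tests is generic, follows one about baseline characteristics, ends with a flexible qualifier, and sits in a section that places all analyses under an SAP that is not at hand. Modelling of exploratory outcomes is ordinary SAP content. Part of this stands: silence on a longitudinal model is not in itself a fault. But the protocol is not silent on the test. It names one and no alternative. The details it specifically defers are sample size, sensitivity analyses and missing data, not this choice. If the sentence covered baseline variables only, objective 2 would have no stated method, and the tests would compare baseline values between randomised arms. Either way the sentence needs attention.

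A reader might infer something stronger: that four vital signs and two EIT measures at five time points mean 6 × 5 = 30 tests, with a chance of 1 − 0.95³⁰ = 79% of at least one false positive. The protocol does not support this. It says the values are recorded, not that each is tested at each time. Respiratory rate, heart rate, arterial pressure and the EIT measures are in no outcome list, and six of the 30 would be T0 comparisons.

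Two further inferences also fail. Separate two-sample tests do not violate any assumption because measurements within a patient are correlated: each uses one value per patient. And it cannot be said that EIT baselines are discarded. Step 2 lists no EIT, and the belt is placed at Step 4, the step in which the assigned oxygen is applied.

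**Conclusion.** The point holds in a limited form. The named tests for continuous outcomes are valid but less precise than an adjusted analysis, and objective 2 has three candidate measures with none designated. The multiplicity at stake is at most about 14%, assuming all three are tested at 0.05 and are independent. The precision forgone is 9% to 49% of the variance for assumed r between 0.3 and 0.7, and it may lie near the lower end because SpO2 is titrated to a target.

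This is a minor point about an outcome listed below the primary and key secondary. The logistic regression and the win ratio are not touched.

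**What to change.** In the Statistical Analysis section:

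- Name one SpO2 measure for objective 2, for example the lowest SpO2 already collected, and treat SpO2 at T1 and T2 as supportive.
- Analyse that measure by ANCOVA with Step 2 SpO2 and site as covariates, with robust or rank-based inference if it is skewed. Confirm that SpO2 is among the Step 2 vital signs.
- State whether T0 is taken before or after the assigned oxygen is started.
- If vital signs at T0 to T4 are compared between arms, use one repeated-measures model per variable, adjusted for the Step 2 value and site. Do not adjust for T0 unless it is stated to precede the assigned oxygen.
- Label these comparisons and the EIT results exploratory.

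The cost is a few sentences and slightly more analysis work. No further data are needed, and the choice should be fixed before outcomes are examined by arm.

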**Secondary Outcome**

Respiratory support escalation within 24 hours post-bronchoscopy will be further evaluated in a prespecified fixed-sequence hierarchical analysis.

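### The multiplicity control credited to the win ratio reaches only its own components; nothing in the protocol links the primary, the key secondary and the other outcomes, and every p<0.05 counts as significant

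*Protocol*

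**What the plan says.** The protocol has three tiers: a primary outcome, one secondary outcome, and six numbered items under Other outcomes.

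- **Primary.** Statistical Analysis: "The primary outcome (escalation of respiratory support within 24 hours) will be analyzed using logistic regression".
- **Key secondary.** Secondary Outcome: "Respiratory support escalation within 24 hours post-bronchoscopy will be further evaluated in a prespecified fixed-sequence hierarchical analysis". Statistical Analysis adds that this is done "using the win ratio method in a prespecified fixed-sequence hierarchical framework to prioritize endpoints and control for multiplicity".
- **Other outcomes.** Several are worded as efficacy questions, for example whether the intervention "reduces the rate of endotracheal intubation at 24 hours, 7 days, and 28 days after bronchoscopy", whether it "improves oxygenation stability, as measured by peripheral oxygen saturation", or whether it "shortens the procedure duration compared with SOT". They are not called exploratory or descriptive.
- **Significance rule.** Two sentences after the multiplicity statement: "All statistical tests will be two-sided, and a p-value <0.05 will be considered statistically significant". No exception is made for any tier.

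The section closes by naming three topics that are detailed in the SAP: sample size, sensitivity analyses and missing data. Multiplicity is not among them.

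**The concern.** Two different devices share similar vocabulary here. A hierarchical composite, such as a win ratio, ranks components within one endpoint and returns one p-value. A fixed-sequence procedure orders separate hypotheses and tests the next one only if the previous one was rejected. Only the second controls error between outcomes. The protocol uses the words of the second for what appears to be the first, and attaches the claim of multiplicity control to it.

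What is at stake is what the trial may claim. As written, a non-significant primary could be followed by a win ratio with p<0.05 that is called significant, with the protocol cited as having dealt with multiplicity. Any one of the other outcomes could likewise be called significant under the general rule, with nothing in the protocol limiting how often that happens by chance.

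**Working it through.** The protocol states no family-wise error rate, sample size or power, so there is no figure of that kind to reproduce. The only numerical input is the 0.05 two-sided threshold.

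**Step 1. What the fixed sequence refers to.** In Secondary Outcome, the phrase describes how escalation itself is evaluated further. In Statistical Analysis, it describes the win ratio for that same outcome. Neither place names a second hypothesis, an order of testing across outcomes, or a condition on the primary result. The sequence is therefore most naturally the ranking of components within escalation.

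**Step 2. Count of tests covered by the 0.05 rule** (from Other outcomes):

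| Item | Comparisons |
|---|---|
| Intubation at 24 hours, 7 days, 28 days | 3 |
| SpO2 during bronchoscopy | at least 1 |
| Procedural interruptions | 1 |
| Procedure duration | 1 |
| ICU and hospital length of stay | 2 |
| Mortality at 28, 60, 90 days | 3 |
| **Total** | **at least 11** |

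Adding the key secondary gives 12, and adding the primary gives 13.

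**Step 3. Chance of at least one false positive, all nulls true, each test at 0.05.** For k independent tests this is 1 − 0.95^k:

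- k = 11: 43.1%
- k = 12: 46.0%
- k = 13: 48.7%

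The Bonferroni upper bound for 13 tests is 13 × 0.05 = 65%.

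The outcomes are correlated, and the repeated time points of intubation and mortality are nested. A simulation of 13 equally correlated normal test statistics (400,000 replicates; the correlation is an assumption) gave:

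| Correlation | At least one false positive |
|---|---|
| 0.3 | 42% |
| 0.5 | 33% |
| 0.7 | 24% |
| 0.9 | 14% |

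**Step 4. Primary plus ungated win ratio only.** If the two were independent, the figure would be 1 − 0.95² = 9.75%. They use the same escalation data, so the real figure is lower. A null simulation assumed 100 patients per arm, a five-level escalation scale with probabilities 0.70/0.12/0.08/0.06/0.04, and 20,000 replicates. The two test statistics had a correlation of 0.98, and at least one was significant in 5.8% of replicates. A smaller simulation (4,000 replicates, again 100 per arm and five levels) gave 6.2% to 6.7%. The excess over 5% is thus about 1 to 2 percentage points.

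**Step 5. What the win ratio does control.** In the 20,000-replicate simulation, the single win-type test rejected in 5.0% of replicates. Testing its four escalation levels separately would have given at least one rejection in about 18%.

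**Step 6. Error after the fix.** Test the primary at 0.05, and the win ratio at 0.05 only if the primary is significant. If the primary null is true, any false claim requires the primary to be rejected, which has probability at most 0.05. If only the win ratio null is true, its own test has probability at most 0.05. The family-wise error for the two is therefore at most 0.05. Keeping all 13 tests confirmatory by Bonferroni would instead need 0.05/13 = 0.0038 for each.

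**The case against.** The strongest reply is that the sentence is partly right and modest in scope. Its subject is the key secondary outcome alone. If controlling multiplicity means avoiding separate tests of each type of escalation, the win ratio does that (Step 5). A reader might infer that the win ratio controls no multiplicity at all, or that the protocol claims it protects the other outcomes. Neither is supported: the first is wrong for the components, and the protocol never makes the second claim. The exposure of the other outcomes comes from the general 0.05 rule, not from the win ratio sentence.

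A reader might also infer that the key secondary merely repeats the primary, since a win ratio on a yes/no outcome equals the inverse of the odds ratio. That identity does not carry over here. The protocol says escalation is assessed hierarchically, and the primary definition lists four kinds of escalation that could be ranked. The two analyses share events and are strongly correlated under the assumed scale, but they are not the same test.

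Finally, the SAP is not shown. It may set a testing order or label the other outcomes exploratory, and the placement of these outcomes in a third tier hints at lower status. This stands as a limit on how far the point goes. It does not remove the point, because the protocol itself makes the multiplicity statement and sets the significance rule. If the SAP already holds a proper order, the protocol's wording would conflict with it and would still need correction.

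**Conclusion.** The point holds in a limited form. The multiplicity statement is true within the win ratio and is not true between outcomes. The text contains no gate from primary to key secondary, and the blanket 0.05 rule applies to the key secondary and at least 11 further comparisons.

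The size depends on which family is meant. For the primary and win ratio alone, the inflation is small: about 6-7% instead of 5%, assuming 100 per arm and a five-level scale. For all 13 tests, it is about 49% under independence, and 14% to 42% under assumed equal correlations of 0.9 to 0.3. A reader might take 49% as the trial's error rate. It is not: it assumes independence, which nested time points rule out, and the actual correlations are unknown. Even at a correlation of 0.9 the figure is well above 5%.

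This should be corrected before analysis, because it changes which results may be called significant.

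**What to change.** In the protocol's Statistical Analysis section:

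1. State that the win ratio avoids multiplicity among its ranked components, and drop any suggestion that it does so across outcomes. Keep the term fixed-sequence for the order of testing.
2. State that the primary is tested at two-sided 0.05, and the win ratio at two-sided 0.05 only if the primary is significant.
3. Restrict the p<0.05 significance rule to these two tests. Report everything under Other outcomes as estimates with 95% confidence intervals and no significance claim.
4. Align the Secondary Outcome wording and the SAP with this.

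The cost is a few sentences and no change to data collection. The price is in claims: none of the other outcomes can be confirmatory, and neither can the win ratio if the primary fails.
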